### Phase 3: Pilot test 2 (pretest-posttest evaluation)

The overall aim of Pilot 2 is to field test the PtDA in the clinical setting. While the Cochrane review [14] of PtDAs demonstrated the general effectiveness of such tools for a) improving patients’ knowledge of the probable outcomes of various treatment options, b) changing patients initial treatment decisions/inclinations once relative risks were accurately perceived, and c) improving patients’ comfort and level of involvement with decision making, several questions remain. Clinical contextual factors may impact the effectiveness of a PtDA and will be taken into account, including the willingness of health care providers (HCPs) to use these tools, HCPs’ level of skill in shared decision making, and effectiveness of systems for decision support implementation. Operating in concert with such factors are the individual values and preferences which patients, and HCPs alike, bring to the clinical encounter. The degree to which these values and preferences are congruent with chosen treatment options varies [14]. Understanding these factors requires not only examination of PtDA effectiveness, but also the context of implementation and HCP-patient interactions during this process. We will therefore employ a combination of summative and formative research methods in Pilot 2.

While the Ottawa Decision Support Framework [15] guides our overall process for designing and testing the decision support tool, our conceptualization of Pilot-2 is also guided by the Ottawa Model of Research Use (OMRU) [42]; there are several elements of the OMRU that are conceptually consistent with the Ottawa Decision Support Framework. OMRU is an interactive model designed for the evaluation of KT innovation implementation. Within the OMRU [42] there are six key elements that interface to determine the process of knowledge translation: 1) evidence-based innovation, 2) potential adopters, 3) the practice environment, 4) implementation of interventions, 5) adoption of the innovation, and 6) outcomes of innovation implementation. In the context of Pilot-2, the innovation is the PtDA, the potential adopters are our participating HCPs and RFA patients, and the practice environment will constitute our Pilot 2 settings.

#### Primary purpose

The primary purpose is to determine the appropriateness and acceptability of the PtDA for our key effectiveness outcomes including decisional conflict (*primary outcome*) and knowledge of treatment options, and choice predisposition (*secondary outcomes*). This pilot test will allow us to determine the effect size of the PtDA, which will inform the required sample size for a randomized controlled trial (RCT) of the effectiveness of the tool as an intervention.

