#### Sample and setting

Pilot 2 will involve a convenience sample of 20 RFA patients from two, large urban cardiac centres in Southern Ontario, Canada. Two centres will be used to allow for examination of differences in contextual factors that may impact the effectiveness of the PtDA. Those eligible will include patients who a) are diagnosed with RFA [15], b) require, and have not yet undergone, a specific treatment for RFA [15], c) have an appointment booked to speak with a site-designated HCP about treatment options within the study period, and d) are able to read, speak, and understand English. This sample size was chosen based on Hertzog’s recommendation [41] of a minimum of 20 participants for single sample pre-post pilot studies used to develop both estimates of effect size and variance for a RCT. larger trial. In addition, based on Cochrane data [14], we anticipate that for a level of significance of alpha = 0.05, power (1-beta) = 0.80, a standard deviation of 0.81, and a correlation between pretest and posttest scores of 0.80, we will be able to detect a difference of 0.34 in decisional conflict scores (range: 1–5). This represents a moderate effect size [43], which is typical of PtDAs [14] and also clinically meaningful given that it is has been observed between those who make decisions versus those who delay decisions [44].

As guided by OMRU [42], our implementation, structured adoption (for the purposes of pilot testing), and outcome evaluation will be as follows:

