#### Field test procedure and outcomes

As an integrated KT strategy involving stakeholders from the inception of this project, Pilot 2 site co-investigators and collaborators are assisting us to establish site-designated HCPs, who will assist us with recruitment. These HCPs will be oriented to the study and procedures for pilot testing the PtDA during scheduled visits with their patients enrolled in the study. Potentially eligible patients, identified by these HCPs, will be asked if they would be willing to speak to the RC about the study. If verbal consent is obtained, contact information will be sent to the RC via telephone. The RC will then phone the referred individual to confirm eligibility, provide a detailed study explanation, and obtain preliminary verbal consent. Eligible patients agreeing to participate will be asked for baseline demographic information via phone interview. They will receive the study explanation, and two copies of the consent form; a postage-paid, addressed envelope will be included to return one signed consent form to the RC. Approximately 1 month prior to their scheduled visits with a site-designated HCP, the RC will conduct pre-test data collection via telephone interview, using our pre/post-test questionnaires. These instruments are designed to assess knowledge about treatment options, decisional conflict, and predisposition about treatment options. Upon completion of baseline data collection, the RC will mail participants a copy of the decision support tool. Participants will be asked to review the decision support tool and arrangements will be made for them to complete the PtDA Acceptability Questionnaire via telephone with the RC.

A paper-based version of the decision support tool will be implemented during participants’ scheduled visits with their site-designated HCPs. Where permission is granted (by participants and site-HCPs), the RC will make arrangements for these sessions to be audio-taped and later, transcribed verbatim. While discussing/deliberating treatment options, participants will be encouraged to share their thoughts on the decision support tool, ask questions about the available RFA treatment options, and discuss any concerns that they may have. This iterative approach supports the interactive principles of integrated knowledge translation [45-47]. One week following these scheduled visits, the RC will conduct post-test outcome assessment via telephone interviews, using our pre/post-test questionnaires.

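### Pilot 2's uncontrolled pre-post change cannot give the effect size of the decision aid, and should not be carried into the RCT as its target difference

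*Protocol article*

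**What the plan says.** The protocol article, Phase 3, Primary purpose, states: "This pilot test will allow us to determine the effect size of the PtDA, which will inform the required sample size" for an RCT of the tool. Phase 3, Sample and setting, repeats the aim when it justifies the number of patients by a recommendation of "a minimum of 20 participants for single sample pre-post pilot studies used to develop both estimates of effect size and variance for a RCT".

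The sequence is given under Field test procedure and outcomes:

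1. Pre-test by telephone, about one month before the visit.
2. The aid is mailed, and then "arrangements will be made for them to complete the PtDA Acceptability Questionnaire via telephone with the RC". No outcome measure is repeated at this point, and the call is not fixed to fall before the visit.
3. The aid is used inside the consultation with the health care professional. Under Sample and setting, having that appointment already booked is an eligibility criterion.
4. "One week following these scheduled visits, the RC will conduct post-test outcome assessment via telephone interviews". This is the only post-test for decisional conflict, knowledge and predisposition.

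Data management and analyses compares pre with post by a paired t-test or the Wilcoxon signed-rank test. There is no comparison group. The article nowhere says that the change also reflects the consultation or elapsed time, and nowhere limits the pilot's contribution to variance and feasibility.

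**The concern.** An RCT of the aid needs a between-group contrast: what patients gain with the aid over what they would gain without it. A single group measured before and after gives only the first part. Here the interval also contains a consultation whose purpose is to discuss treatment options, which these patients would have attended in any case. Some fall in decisional conflict and some rise in knowledge are plausible after such a visit with no aid at all.

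Supplying an effect size for the RCT is a declared purpose of Pilot 2. If the raw change is read as the effect of the aid and used as the RCT target difference, the RCT is likely to be planned too small.

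**Working it through.** **1. The pilot's own calculation.** Inputs from Phase 3, Sample and setting: n = 20, "level of significance of alpha = 0.05, power (1-beta) = 0.80, a standard deviation of 0.81" and "a correlation between pretest and posttest scores of 0.80".

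- SD of change = 0.81 × √(2 × (1 − 0.80)) = 0.512.
- Paired t-test, 19 degrees of freedom, two-sided 0.05 (sidedness is not stated; two-sided reproduces the figure): the difference detectable with 80% power is 0.338, and power at 0.34 is 80.4%.

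The stated 0.34 is correct. The point concerns what the estimate means, not this arithmetic.

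**2. What the change contains.**

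- Pilot change = aid (including its use in the visit) + consultation + about five weeks (approximately one month plus one week) + regression to the mean, to whatever extent patients enter at a time of high conflict.
- RCT contrast, if controls also have the consultation = (aid + consultation + time + regression) − (consultation + time + regression) = aid.

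The two differ by the change that would occur under consultation alone. Pilot 2 never observes that quantity, so the paired analysis cannot remove it. The RCT comparator is not stated. Consultation without the aid is an assumption, consistent with Patient decision aids, which describes such tools as additions to consultation and cites evidence against routine counselling.

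**3. Illustration of the consequence.** The documents give no figure for the non-tool share f, so 25%, 50% and 75% are assumed. For an RCT sized at two-sided 0.05 and 80% power on the full change, the SD cancels:

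- Power = Φ((1.96 + 0.8416)(1 − f) − 1.96)
- Sample size multiple = 1/(1 − f)²

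| f | Argument of Φ | Power | Multiple of N |
|---|---|---|---|
| 25% | 2.8016 × 0.75 − 1.96 = 0.141 | 56% | 1.8 |
| 50% | 2.8016 × 0.50 − 1.96 = −0.559 | 29% | 4 |
| 75% | 2.8016 × 0.25 − 1.96 = −1.260 | 10% | 16 |

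Rounding the RCT up to whole patients moves the last power to between 10% and 11%.

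The absolute numbers depend on the analysis. Suppose, purely as an example, that the full change were 0.34 with SD 0.81. Comparing post-scores, n per arm = 2 × (1.96 + 0.8416)² × 0.81² / d². This gives 90 at d = 0.34, then 159, 357 and 1,426 at d = 0.255, 0.17 and 0.085. Adjusting for baseline with correlation 0.80 multiplies the variance by 1 − 0.80² = 0.36 and gives 33, 58, 129 and 514. The relative loss is the same either way.

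**The case against.** **The aid is meant to work within the consultation.** Patient decision aids presents such tools as supplements to consultation, and the field test uses the aid in the visit. A post-visit score therefore measures the intervention as delivered. This stands. A reader might infer that measuring after the visit is itself a mistake; the documents do not support that. The gap is the missing comparator.

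**The article promises only to inform the RCT.** It does not fix the RCT target difference or make the pilot its sole basis, and it also plans variance and correlation estimates, which need no control group. This stands and limits the seriousness. It does not rescue the claim that the effect size of the aid will be determined.

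**Context is examined.** Audio-taped visits, patient interviews and focus groups address how the aid is used. These analyses are qualitative and yield no number that separates the components.

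**The 0.34 may already be a controlled contrast.** The article says "we will be able to detect a difference of 0.34 in decisional conflict scores", so it is a detectable difference and not a predicted change. It is tied to a systematic review that the article describes as comparing aids with routine counselling. This stands: 0.34 is used above only as an example, and nothing shows that it should be discounted.

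**Choice quality.** A reader might infer that reaching any decision lowers the Decisional Conflict Scale score through its choice-quality component, so that those items should be dropped. The Decisional conflict scale section gives no item allocation and no scoring rule for patients yet to choose. Lower conflict is also what the aid is meant to achieve. That change is not justified by the documents.

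**Conclusion.** The concern holds in this form: Pilot 2 can describe within-group change with the aid plus consultation, but it cannot determine the effect size of the aid or supply the effect size for the RCT. This follows from the design alone and needs no assumption.

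That the change overstates the RCT contrast is probable, not certain. It assumes that the control arm has the consultation and that consultation and time by themselves reduce conflict; the article has no data on either. A reader might go further and infer that the RCT will be under-powered by a known amount. The documents do not support this: the shares of 25%, 50% and 75% are assumed, and the RCT's planning is not described. The power figures (about 56%, 29% and 10-11%) show only how sensitive the RCT would be.

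The pilot's sample size calculation is sound, and its SD and pre-post correlation remain usable. The point should be fixed, but it does not prevent Pilot 2 from running.

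**What to change.** **Wording, the essential change.** In Phase 3, Primary purpose, and in the matching sentence of Sample and setting, call the result *within-group pre-post change with PtDA plus consultation*. Then state that:

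- this change will not be used as the RCT target difference;
- the RCT will be sized on a prespecified, clinically meaningful between-group difference or on controlled evidence;
- the pilot will supply the SD, the pre-post correlation and feasibility data.

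This costs a few sentences and a minor ethics amendment. Study status reports that Pilot 1 is still enrolling, so the change can be made before Pilot 2 begins.

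**Optional.** Repeat the outcome measures on the Acceptability Questionnaire call, and fix that call to fall after the aid has been reviewed and before the visit. Report the result as *pre-consultation change*. It would separate out the consultation, but it should not be labelled an effect of the aid: time and regression to the mean remain, and use of the aid in the visit is left out. The cost is a few more minutes for each participant and one more exposure to the questionnaires.

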#### Secondary purpose

The secondary purpose is to a conduct a formative evaluation of the use of PtDA while in use. This evaluation will allow us to conduct a preliminary assessment of predisposing, enabling, and reinforcing factors [42] which may impact the ability of the tool to effectively translate knowledge about various treatment options, and support informed decision making, within the clinical context.

#### Sample and setting

Pilot 2 will involve a convenience sample of 20 RFA patients from two, large urban cardiac centres in Southern Ontario, Canada. Two centres will be used to allow for examination of differences in contextual factors that may impact the effectiveness of the PtDA. Those eligible will include patients who a) are diagnosed with RFA [15], b) require, and have not yet undergone, a specific treatment for RFA [15], c) have an appointment booked to speak with a site-designated HCP about treatment options within the study period, and d) are able to read, speak, and understand English. This sample size was chosen based on Hertzog’s recommendation [41] of a minimum of 20 participants for single sample pre-post pilot studies used to develop both estimates of effect size and variance for a RCT. larger trial. In addition, based on Cochrane data [14], we anticipate that for a level of significance of alpha = 0.05, power (1-beta) = 0.80, a standard deviation of 0.81, and a correlation between pretest and posttest scores of 0.80, we will be able to detect a difference of 0.34 in decisional conflict scores (range: 1–5). This represents a moderate effect size [43], which is typical of PtDAs [14] and also clinically meaningful given that it is has been observed between those who make decisions versus those who delay decisions [44].

As guided by OMRU [42], our implementation, structured adoption (for the purposes of pilot testing), and outcome evaluation will be as follows:

#### Field test procedure and outcomes

As an integrated KT strategy involving stakeholders from the inception of this project, Pilot 2 site co-investigators and collaborators are assisting us to establish site-designated HCPs, who will assist us with recruitment. These HCPs will be oriented to the study and procedures for pilot testing the PtDA during scheduled visits with their patients enrolled in the study. Potentially eligible patients, identified by these HCPs, will be asked if they would be willing to speak to the RC about the study. If verbal consent is obtained, contact information will be sent to the RC via telephone. The RC will then phone the referred individual to confirm eligibility, provide a detailed study explanation, and obtain preliminary verbal consent. Eligible patients agreeing to participate will be asked for baseline demographic information via phone interview. They will receive the study explanation, and two copies of the consent form; a postage-paid, addressed envelope will be included to return one signed consent form to the RC. Approximately 1 month prior to their scheduled visits with a site-designated HCP, the RC will conduct pre-test data collection via telephone interview, using our pre/post-test questionnaires. These instruments are designed to assess knowledge about treatment options, decisional conflict, and predisposition about treatment options. Upon completion of baseline data collection, the RC will mail participants a copy of the decision support tool. Participants will be asked to review the decision support tool and arrangements will be made for them to complete the PtDA Acceptability Questionnaire via telephone with the RC.

A paper-based version of the decision support tool will be implemented during participants’ scheduled visits with their site-designated HCPs. Where permission is granted (by participants and site-HCPs), the RC will make arrangements for these sessions to be audio-taped and later, transcribed verbatim. While discussing/deliberating treatment options, participants will be encouraged to share their thoughts on the decision support tool, ask questions about the available RFA treatment options, and discuss any concerns that they may have. This iterative approach supports the interactive principles of integrated knowledge translation [45-47]. One week following these scheduled visits, the RC will conduct post-test outcome assessment via telephone interviews, using our pre/post-test questionnaires.

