#### Procedure

The research process will be governed centrally. Each clinical site has a running list of known RFA patients. Designated third-party clinicians at each site will ask eligible patients if they would be willing to speak to the RC about the study. If verbal consent is obtained, contact information will be sent to the RC via telephone (to preserve confidentiality). The RC will then phone the referred individual to confirm eligibility, provide a detailed study explanation, and obtain preliminary verbal consent. Eligible patients agreeing to participate will be asked for baseline demographic information via phone interview. They will receive the study explanation, two copies of the consent form, and the draft decision support tool in the mail; a postage-paid, addressed envelope will be included to return one signed consent form to the RC. Participants will be asked to take 1–2 weeks to review the PtDA. The RC will schedule a follow-up phone call wherein participants will be asked to complete a PtDA Acceptability Questionnaire via phone interview; this process will take approximately 10–15 minutes. The RC will collate the data from this acceptability pilot and appropriate revisions will be made to the PtDA. A maximum of 5 participants per site is required. Based on up-front consultation with our clinical sites, we foresee no difficulty in obtaining the required sample.

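### In Pilot 2 the HCPs who deliver the decision aid also identify which of their own patients are put forward, and nothing requires every eligible booked patient to be approached

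*Protocol article*

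**What the plan says.** All references are to the protocol article, Phase 3 (Pilot test 2) unless stated.

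- **Sampling.** Sample and setting: "Pilot 2 will involve a convenience sample of 20 RFA patients from two, large urban cardiac centres in Southern Ontario, Canada".
- **Eligibility.** Of the four criteria in that section, c) is that patients "have an appointment booked to speak with a site-designated HCP about treatment options within the study period".
- **Recruitment.** Field test procedure and outcomes says that site co-investigators and collaborators "are assisting us to establish site-designated HCPs, who will assist us with recruitment". It goes on: "Potentially eligible patients, identified by these HCPs, will be asked if they would be willing to speak to the RC about the study". The research coordinator then phones the referred person, confirms eligibility and seeks verbal consent.
- **Delivery.** Same section: "These HCPs will be oriented to the study and procedures for pilot testing the PtDA during scheduled visits with their patients enrolled in the study", and "A paper-based version of the decision support tool will be implemented during participants’ scheduled visits with their site-designated HCPs".
- **Judging the tool.** Under Post-field test debriefing interviews, site HCPs give their views in one focus group per site on the tool's usefulness and its perceived efficacy for their patients.
- **Use of the results.** Primary purpose says the pilot will give the effect size that informs the RCT's sample size. Sample and setting justifies the 20 patients by the need to estimate effect size and variance.
- **Context.** The introduction to Phase 3 lists factors to be taken into account, "including the willingness of health care providers (HCPs) to use these tools, HCPs’ level of skill in shared decision making" among them.

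**The concern.** The people who deliver the tool, and who are later asked how well it worked, also identify the patients on whom it is tried. The text sets no rule that a patient who meets criteria a) to d) must be approached. An HCP may, without any ill intent, think first of some patients and not of others, for instance by expected interest, literacy, distress or length of visit. The coordinator's eligibility check covers referred patients only, so it cannot show who was left out. The planned missing-data analysis compares presence and absence of scale data, so it concerns participants and cannot show this either.

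Two things are at stake. First, the acceptability results and the effect-size and variance estimates may describe a group that differs from the patients the RCT will recruit. Second, the described route yields no count of eligible patients against which approach and uptake could be expressed, and those rates are useful for planning the RCT.

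**Working it through.** **1. Roles.** Reading the sections side by side:

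| Step | Who acts in Pilot 2 | Where stated |
|---|---|---|
| Identify candidates | Site-designated HCPs | Field test procedure and outcomes |
| Ask the patient | Not specified (passive wording) | Same |
| Confirm eligibility | Research coordinator, referred patients only | Same |
| Use the aid in the visit | Site-designated HCPs | Same |
| Comment on efficacy | Site HCPs, focus groups | Post-field test debriefing interviews |

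No step starts from the full set of eligible patients.

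**2. Can that set be listed?** Criterion c) confines eligibility to patients with a booked visit with a site-designated HCP. Pre-test data are collected about one month before the visit, so bookings are known in time. The article mentions no appointment list. That one can be drawn up is an inference from criterion c).

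**3. The plan's own figure.** Inputs from Sample and setting: n = 20, alpha 0.05, power 0.80, SD 0.81, pre-post correlation 0.80. Sidedness is not stated.

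- SD of the differences = 0.81 × √(2 × (1 − 0.80)) = 0.81 × √0.40 = 0.512.
- Two-sided paired t-test with 19 degrees of freedom (noncentral t): detectable difference 0.338 at 80% power, and power at 0.34 is 80.4%.

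The stated 0.34 is reproduced. Nothing in that calculation depends on how patients are chosen.

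**4. Precision of the pilot estimate.**

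- Standard error = 0.512 / √20 = 0.115.
- 95% half-width = 2.093 × 0.115 = 0.24 points.

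**5. Scale of a selection effect, by assumption only.** The article gives no figure for this. Suppose the HCP's choice correlates c with the patient's change in score, and a fraction f of eligible patients is put forward. The mean change in those chosen then shifts by c × λ × 0.512. Here λ is the standard normal density at the cut-off divided by f.

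- c = 0.1, f = 0.9: λ = 0.195, shift = 0.1 × 0.195 × 0.512 = 0.01.
- c = 0.3, f = 0.5: λ = 0.798, shift = 0.3 × 0.798 × 0.512 = 0.12.

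The sign of c is unknown, so the shift is 0.01 to 0.12 points in either direction under these assumptions. Even the upper end is about half the 0.24 half-width, but a confidence interval does not allow for a shift of this kind. It is not carried through to an RCT sample size, because 0.34 is a within-patient change and a two-arm trial is sized on a between-arm difference.

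**The case against.** The strongest reply is that the article openly declares a convenience sample for a small two-centre pilot, and states nothing false or contradictory. The sentence on identification gives HCPs no licence to pass over eligible patients. It does not even say who asks them. Entry also depends on the patient's agreement and the coordinator's check. A screening log is the kind of detail an article leaves to the full protocol. HCP reluctance is not ignored either: there are HCP focus groups, patient interviews on barriers and on comfort with the HCP, and audio-taped visits where permitted.

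Much of this stands, and it rules out three stronger readings.

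- A reader might infer that the patients are hand-picked. The text leaves that open but does not say it.
- A reader might infer that the effect will be overstated. The direction is not known. Engaged patients might gain more from the tool, or might start with lower decisional conflict and have less room to fall on a scale whose minimum is 1.
- A reader might contrast Pilot 1, where "Designated third-party clinicians at each site will ask eligible patients if they would be willing to speak to the RC about the study", and conclude that a safeguard was given up. Pilot 1 has no HCP-delivered visit, since the tool is mailed and assessed by telephone, so there is no delivery role to separate. It too is a convenience sample with no consecutive rule. The article also does not say that the two Pilot 2 centres are among the eight Pilot 1 centres.

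What the reply does not remove is the recruitment route itself. That is a stated design choice, not a detail left out, and declaring it does not make the estimates fit the planning purpose the article gives them. The focus groups and interviews learn only about patients who were put forward.

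**Conclusion.** The point holds as an avoidable weakness of design, not as an error in a figure. The HCPs who deliver the tool are the route into the sample, no rule requires all eligible booked patients to be approached, and the results are to inform an RCT. Selection is possible, with unknown direction and size. The range of 0.01 to 0.12 points in the working rests wholly on assumed values and serves only to give a scale. At n = 20 random error is large in any case, and consecutive recruitment does not reduce it. Nor does it remove self-selection by patients who decline. It removes one systematic source of doubt at almost no cost and supplies an uptake denominator, so the change should be made. Study status reports Phase 1 complete and Pilot 1 enrolling, so on the article's account Pilot 2 could still be changed.

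**What to change.** In Sample and setting and in Field test procedure and outcomes for Pilot 2, replace the convenience sample with consecutive eligible patients:

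1. At each site, existing clinic staff list all RFA patients with a booked treatment-options visit with a site-designated HCP (criterion c).
2. The HCP only confirms clinical eligibility (criteria a and b). Criterion b) plausibly needs a clinician's judgement, so this step should stay with the HCP.
3. Every patient meeting a) to d) is asked, in order, until 20 are enrolled.
4. An anonymous log records the numbers booked, eligible, approached, declining, and not approached with the reason.

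The cost is a short log and possibly slightly slower recruitment. The sample size of 20 and the detectable difference of 0.34 are unchanged.
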